#### Economic evaluation

The economic evaluation will include a cost-utility analysis from a societal perspective. The time horizon of this evaluation will be the same as the duration of the trial, that is, 12 months. All costs (direct and indirect) related to both interventions will be calculated. The final cost calculation of unit costs will be based on a combined bottom-up and top-down approach. In accordance with Dutch guidelines for cost calculation, indirect healthcare costs will not be taken into account. In addition, resource use will be measured by use of primary data that is registered in our case record forms (CRFs) by use simple checklists. Furthermore, a questionnaire will be used to survey the direct non-healthcare costs related to travelling, impaired mobility and domiciliary care (for normal daily activities). The incremental, indirect non-healthcare costs per QALY gained will be based on the utility scores from the EQ-5D [39-41]. For all direct healthcare costs, the unit prices will be based either on prices from the hospital financial department or the Dutch guidelines for cost calculation [45].

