#### Hospital and societal costs

The economic evaluation will include a cost-utility analysis from a Dutch societal perspective. The incremental costs per quality adjusted life year (QALY) gained will be based on utility scores from the EQ-5D [39-41]. All hospital expenses (direct and indirect) related to both interventions will be monitored. In addition, a cost questionnaire offered at the regular follow-up consultation (3, 6 and 12 months) will help assess the societal and individual costs outside health care relating to patients’ absence, impaired mobility, work, or normal daily activities. Unit prices will be based either on prices from the participating hospital financial departments or will be extrapolated using Dutch guidelines for cost calculation [45].

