#### Descriptive statistics

The primary outcome parameter of time to functional recovery and the secondary parameter of LOS in hospital will be given in days, with a median and range. Morbidity will be classified according to the classification described by Dindo *et al*. and defined as a dichotomous composite endpoint, while readmission will be given as a percentage. Scores for quality of life, body image and cosmesis will be given as mean and standard deviation per time point per treatment arm. Hospital costs will be given as median and range. Long-term incidence of incisional hernia will be reported and analysed.

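### The Economic evaluation section words the cost-utility numerator as indirect non-healthcare costs only, contradicting the unrestricted ratio and the all-costs societal perspective stated elsewhere

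*Protocol article*

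**What the plan says.** The protocol article describes the cost-utility analysis in two places.

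- **Hospital and societal costs** (under the endpoints): "The incremental costs per quality adjusted life year (QALY) gained will be based on utility scores from the EQ-5D". The numerator is not limited to any cost category, and the perspective is Dutch societal.
- **Economic evaluation** (under Statistical analysis): "The incremental, indirect non-healthcare costs per QALY gained will be based on the utility scores from the EQ-5D". Here the numerator is one category.

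The rest of the Economic evaluation section is broad. It says "The economic evaluation will include a cost-utility analysis from a societal perspective" and "All costs (direct and indirect) related to both interventions will be calculated". It makes one exclusion, citing the Dutch costing guidelines: "indirect healthcare costs will not be taken into account". It collects a second category ("a questionnaire will be used to survey the direct non-healthcare costs related to travelling, impaired mobility and domiciliary care") and values a third ("For all direct healthcare costs, the unit prices will be based either on prices from the hospital financial department"). The horizon is 12 months.

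Separately, the Descriptive statistics section says: "Hospital costs will be given as median and range".

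**The concern.** The sentence that names the numerator stands in the analysis section, where an analyst would look for the rule. Followed as worded, it drops theatre time, equipment, consumables, bed-days and readmissions from the cost side of the ratio. Those are the items that a change of surgical approach affects most directly. The Discussion describes the expected trade-off in these terms, with shorter operating time set against spending on technology and consumables. A ratio without these items would not address that trade-off.

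Two analysts working from the same article could therefore compute different ratios, each able to cite a sentence in support. Hospital and societal costs over 1 year are a listed secondary endpoint, so the result would be reported and used.

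**Working it through.** The documents give no cost, QALY or cost-per-QALY figure, so there is nothing of the plan's own to reproduce. The check compares the texts and then illustrates the consequence with assumed inputs.

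**1. Cost categories, side by side**

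| Category | Elsewhere in the article | In the numerator as worded in Economic evaluation |
|---|---|---|
| Direct healthcare | Monitored and priced | No |
| Direct non-healthcare | Surveyed by questionnaire | No |
| Indirect non-healthcare | Follow-up cost questionnaire covers absence and work | Yes |
| Indirect healthcare | Explicitly excluded | No |

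A societal numerator that applies the stated exclusion contains the first three rows. The sentence names only the third.

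**2. Can the difference change the answer?**

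Let dH, dN and dI be the mean differences, laparoscopic minus open, in direct healthcare (hospital), direct non-healthcare and indirect non-healthcare cost. Let dQ be the QALY difference.

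- Full ratio = (dH + dN + dI) / dQ
- Restricted ratio = dI / dQ

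The signs differ when dH + dN is opposite in sign to dI and larger in absolute size. All inputs below are assumptions, in arbitrary currency units, with dQ from 0.01 to 0.05.

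| dH, dN, dI | Sum | Full ratio (dQ 0.01 to 0.05) | Restricted ratio (dQ 0.01 to 0.05) |
|---|---|---|---|
| +1000, -100, -500 | +400 | +40,000 to +8,000 | -50,000 to -10,000 |
| +2000, 0, -500 | +1500 | +150,000 to +30,000 | -50,000 to -10,000 |
| -1000, -100, -500 | -1600 | -160,000 to -32,000 | -50,000 to -10,000 |

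For the first row, 400 / 0.01 = 40,000 and 400 / 0.05 = 8,000, against -500 / 0.01 = -50,000 and -500 / 0.05 = -10,000. In the first two rows the full ratio shows a cost per QALY gained, while the restricted ratio shows laparoscopy as both cheaper and better. In the third row the sign agrees, but the restricted numerator captures only 500 of the 1600 saved.

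**3. The descriptive summary of hospital costs**

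An incremental cost is a difference in arithmetic means. Component means add up to the mean total, whereas medians in general do not. If costs are lognormal (an assumption), median / mean = 1 / sqrt(1 + CV²), which is 0.894, 0.781 and 0.707 for assumed CVs of 0.5, 0.8 and 1.0. Within an arm the median then lies 11%, 22% or 29% below the mean. If both arms share the same CV, the difference in medians is the difference in means multiplied by that one factor, so its sign is unchanged.

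**The case against.** The strongest reply is that this is an editing slip. The disputed sentence closely follows the one under Hospital and societal costs with a qualifier inserted, and what it asserts is the source of the utilities. The sentences around it take a societal perspective and price direct healthcare, so an informed analyst would probably use all the costs. That is plausible, though it is an inference. It also concedes that the sentence is wrong as it stands. Because the sentence sits in the analysis section and contradicts other text, it is not detail left to an analysis plan.

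Three stronger readings are tempting, and the documents do not support them.

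- *The economic question cannot be answered.* It can. Hospital costs, non-healthcare costs, EQ-5D utilities and a 12-month horizon are all planned.
- *Medians will be used in the ratio, biasing or reversing it.* No section says so. The median and range stand under Descriptive statistics. The primary outcome is also described there by median and range, yet it is analysed by regression. The 11% to 29% gaps are within-arm figures from assumed CVs, and at equal CV they cannot reverse a comparison. The choice of cost estimator and interval may properly be left to a fuller document.
- *Calculating all costs contradicts leaving out indirect healthcare costs.* This reads as a general statement followed by one named exclusion with its basis given.

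**Conclusion.** The point holds as an internal contradiction on a secondary endpoint. The Economic evaluation section states a numerator that conflicts with the Hospital and societal costs section and with its own perspective and scope. Taken literally, it omits two of the three cost categories that belong in the ratio.

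The actual size of the effect cannot be derived from the documents. Under the assumed inputs above, the ratio moves from between +8,000 and +40,000 to between -10,000 and -50,000 per QALY, so a change of sign is possible but not certain. It requires the combined direct cost difference to oppose, and exceed, the indirect non-healthcare difference. The primary outcome, sample size and data collection are unaffected. The wording should be corrected before the economic analysis is run.

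**What to change.** In the Economic evaluation section, replace the restricted wording with one definition: the numerator is the between-arm difference in mean total societal cost over 12 months, made up of direct healthcare, direct non-healthcare and indirect non-healthcare costs, with indirect healthcare costs left out as already stated. The denominator remains the between-arm difference in QALYs from EQ-5D utilities. Use the same definition in the Hospital and societal costs section.

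As a supporting improvement, add to the Descriptive statistics section the arithmetic mean hospital cost per arm and a confidence interval for the difference, keeping the median and range as description. The reported summary would then show the quantity that an incremental cost is built from.

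The cost is a change of wording and one additional summary. No new data, patients or follow-up are needed.

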#### Registry

The prospective registry of patients who cannot be randomised because of ineligibility or because of explicit treatment preference on the part of the patient or surgeon will be analyzed as an observational study. In addition, data from the registry will be analyzed for interaction between treatment, centre, and study type (randomised or not). On condition that there is no interaction between treatment, centre, and study type, and that the observational study does not suffer from severe confounding (because adjusting for that strongly reduces the power of the observational study), pooling of both studies should give more power than separate analyses of either study. Possible confounders will be registered in the CRFs. The inclusion of the prospective registry in the trial design will create an uninterrupted case series, which will increase external validity and generalisability.

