**Methods:**

Patients eligible for left lateral sectionectomy (LLS) of the liver will be recruited and randomised at the outpatient clinic. All randomised patients will undergo surgery in the setting of an ERAS programme. The experimental design produces two randomised arms (open and laparoscopic LLS) and a prospective registry. The prospective registry will be based on patients that cannot be randomised because of the explicit treatment preference of the patient or surgeon, or because of ineligibility (not meeting the in- and exclusion criteria) for randomisation in this trial. Therefore, all non-randomised patients undergoing LLS will be approached to participate in the prospective registry, thereby allowing acquisition of an uninterrupted prospective series of patients. The primary endpoint of the ORANGE II trial is time to functional recovery. Secondary endpoints are postoperative LOS, percentage readmission, (liver-specific) morbidity, QOL, body image and cosmetic result, hospital and societal costs over 1 year, and long-term incidence of incisional hernias. It will be assumed that in patients undergoing laparoscopic LLS, length of hospital stay can be reduced by two days. A sample size of 55 patients in each randomisation arm has been calculated to detect a 2-day reduction in LOS (90% power and α = 0.05 (two-tailed)).

The ORANGE II trial is a multicenter randomised controlled trial that will provide evidence on the merits of laparoscopic surgery in patients undergoing LLS within an enhanced recovery ERAS programme.

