### Study design

The ORANGE II trial is a prospective superiority study with an experimental design, using two double-blinded randomised controlled arms and a prospective registry to determine whether laparoscopic surgery is to be preferred over open surgery in patients undergoing a LLS and participating in an enhanced recovery programme. In the participating randomising centers, patients, nurses and the ward physician (but not the operating surgeon) will be blinded for the type of intervention up to and including postoperative day (POD) 3. They will record the functional recovery criteria twice daily. Only the investigator and operating surgeons will know the actual procedure. The blinded ward physician(s) will decide on whether a patient will be discharged or not.

However, randomisation of patients undergoing open or laparoscopic liver resection is hazardous as previously explained. Moreover, another potential source of bias exists when randomising patients with a strong treatment preference. When patients cannot be blinded to their treatment allocation (POD 3) they may be resentful and demoralised if they do not receive their preferred treatment, and consequently they may have poor compliance. By contrast, patients receiving their preferred treatment may have above-average compliance.

Thus to capitalise on centres both with and without preference for laparoscopic liver surgery, and thereby to acquire an uninterrupted prospective series of patients, all non-randomised patients undergoing a LLS will be approached to participate in the prospective registry. Registration of these patients is imperative to guarantee a consecutive series of patients and also because the absence of such a series may restrict generalisation of the results, as randomised participants may not in fact be representative [36]. The combination of an RCT and a prospective registry will improve overall power and strengthen the external validity and generalisability of study results [33-35]. This non-randomised registry group will be analysed for centre and centre by treatment interaction as an observational study. Medical centres that wish to participate in this trial, but with liver surgeons early in the laparoscopic learning curve, will be accompanied during the procedure by an experienced proctoring laparoscopic HPB-surgeon.

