### Study population

Every patient requiring an LLS will be identified and informed at the outpatient clinic about open and laparoscopic liver resection. Only patients meeting the inclusion and exclusion criteria will be approached for randomisation. After reading the ORANGE II trial patient information and being allowed 1 week for consideration, patients will be asked for their informed consent. All patients ineligible for randomisation will be approached for participation in the prospective registry. If patients express an explicit preference, they will be allocated to the prospective registry and interviewed to ascertain the reasons for their preferences. Personal written informed consent will be obtained for all groups. Randomisation will be carried out through the ORANGE II trial website using web-based randomisation software (TENALEA®; www.tenalea.com) (see Figure 1 for trial flow-chart).

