**Figure 1 F1:**
[figure not shown]
Orange II-Trial Flowchart.

Patients will be approached for randomised inclusion if they meet each of the following inclusion criteria: require LLS; willingness to participate in the study; able to understand the nature of the study and what will be required of them; are men or non-pregnant, non-lactating women between the ages of 18 and 80 years of age; have a body mass index of between 18 and 35; and have ASA grading of I to III.

The exclusion criteria are: liver resection other than LLS; underlying liver disease; unwillingness to participate; inability to give written informed consent; and ASA grading of IV to V.

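### The study-type test and the pooling rule use one randomised-or-not factor, although the registry mixes ineligible patients with those kept out by preference

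*Protocol article*

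**What the plan says.** The Methods paragraph of the abstract admits patients to the registry because of an explicit preference of patient or surgeon, "or because of ineligibility (not meeting the in- and exclusion criteria) for randomisation in this trial". The Study population section repeats the second route: "All patients ineligible for randomisation will be approached for participation in the prospective registry". The Registry section describes a single group, "patients who cannot be randomised because of ineligibility or because of explicit treatment preference on the part of the patient or surgeon".

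The planned comparison with the trial is that "data from the registry will be analyzed for interaction between treatment, centre, and study type (randomised or not"). Pooling is allowed when this interaction is absent and confounding is not severe. Possible confounders are to be recorded in the CRFs.

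The Study design section explains why the registry exists: "Registration of these patients is imperative to guarantee a consecutive series of patients", and "the absence of such a series may restrict generalisation of the results, as randomised participants may not in fact be representative".

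The criteria stand under Study population, after Figure 1. Randomisation requires age 18 to 80, BMI 18 to 35 and ASA I to III. The exclusions are resections other than LLS, underlying liver disease, "unwillingness to participate; inability to give written informed consent; and ASA grading of IV to V". On consent, Study population states: "Personal written informed consent will be obtained for all groups".

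**The concern.** The two routes into the registry raise different questions. Eligible patients with a preference show whether the treatment effect differs in people who could have been randomised but were not. Ineligible patients show whether the effect extends beyond the trial's criteria. A single randomised-or-not factor answers neither question separately.

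Eligibility could plausibly modify the effect on this endpoint. Functional recovery requires, among other things, bilirubin and INR that are normal or falling, and independent mobility. Patients with underlying liver disease or ASA IV to V may differ in these respects, and by design they can appear only in the registry.

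Two things are at stake: how the study-type interaction is read, and who enters a pooled estimate if pooling goes ahead.

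**Working it through.** **1. The passages side by side**

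- Entry: the abstract, Study population and Registry sections agree that ineligible patients and preference patients share one registry.
- Contrast: the Registry section defines study type as two-valued. It names no eligibility term and no restriction to eligible registry patients.
- Consequence: the non-randomised level combines preference or selection with failure of the criteria, so the treatment × study-type term combines both.
- Adjustment: entering recorded confounders as main effects corrects for different baseline recovery times. It does not remove a different *treatment effect* in ineligible patients. That needs a treatment × eligibility term or restriction to eligible patients.
- Pooling: absence of severe confounding is a different condition from absence of effect modification, so it does not close the gap.

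**2. The plan's own figures, used below for scale**

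Inputs from the Sample size section: 2-day reduction, SD 2.73, two-sided α = 0.05, power 90%.

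- n per arm = 2 × (1.960 + 1.282)² × 2.73² / 2² ≈ 39.2, so 40, as stated.
- 40 / 0.9 = 44.4, so 45. Adding one per arm for each of 10 centres gives 55 per arm, or 110 in total, as stated.

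These figures reproduce and are not in dispute.

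**3. Illustration of the mechanism (assumed values)**

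The article gives neither the share q of ineligible registry patients nor the effect e in them. Assume 2 days in all eligible patients, randomised or not, and the same split between approaches in both registry subgroups. Then

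registry effect = (1 − q) × 2 + q × e

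| q | e (days) | registry effect | gap to trial |
|---|---|---|---|
| 0.2 | 0 | 1.6 | 0.4 |
| 0.2 | 1 | 1.8 | 0.2 |
| 0.4 | 0 | 1.2 | 0.8 |
| 0.4 | 1 | 1.6 | 0.4 |
| 0.6 | 0 | 0.8 | 1.2 |
| 0.6 | 1 | 1.4 | 0.6 |

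In every row the gap comes from eligibility alone, with no effect of preference. If e = 2, the gap is 0.

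The reverse is also possible. With 2.5 days in eligible preference patients and 1 day in an ineligible third, the registry effect is (2/3) × 2.5 + (1/3) × 1 = 2.0 days. It matches the trial although neither subgroup does.

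**4. What the interaction test could detect**

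Assume 50 per arm analysed in the trial (about 55 × 0.9), m per arm in the registry (m is not given) and SD 2.73 throughout:

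SE = 2.73 × √(2/50 + 2/m)

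- m = 25: SE = 0.946; power 7% for a 0.4-day difference and 25% for 1.2 days.
- m = 100: SE = 0.669; power 9% for 0.4 days and 43% for 1.2 days.

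So a non-significant result would be weak evidence that ineligible patients can be pooled with the trial.

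**The case against.** The strongest reply concerns the target population. The Study design section approaches all non-randomised LLS patients and can be read as taking all LLS patients as the reference. For that reference, ineligible patients belong in the comparator, and a gap caused by them is a real limit on generalisation. This stands. A reader might infer that the registry cannot show whether randomised patients are representative, or that any gap in the table is false. The documents support neither. What the two-valued factor cannot do is separate the sources of a difference, or speak for the eligible population alone.

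Second, planned data may allow the separation. ASA grade, P-POSSUM, patient characteristics and possible confounders are recorded, and patients with a preference are interviewed about their reasons. An eligibility field may already be in the CRF. This also stands, and it makes the remedy cheap. But the stated analysis does not use the distinction.

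Third, a three-level factor might be called a detail for the analysis plan. That would hold if the article were silent. It instead defines the factor itself, with two values, and makes pooling depend on it.

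Fourth, on completeness of the series, a reader might count two exclusion criteria as barring the registry. Unwillingness bars only those who refuse the study altogether, since patients with an explicit preference are sent to the registry. Inability to give written consent is a clear bar. The article discloses the consent requirement, and every consent-based registry loses refusers, so this is a matter of wording.

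**Conclusion.** The point holds for the interaction analysis and the pooling rule. As specified, a treatment × study-type difference or its absence cannot be assigned to preference and selection rather than to ineligibility, and a pooled estimate could include patients whom the trial excludes.

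Its reach is limited. The comparison between the randomised arms is unaffected, the separate observational analysis of the registry can still be done, and a descriptive comparison with all consenting LLS patients stays valid. A spurious interaction would merely prevent pooling; a masked one would permit it.

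No size can be given from the documents. The gaps of 0.2 to 1.2 days and the power of 7% to 43% rest on assumed shares, subgroup effects and registry sizes. They show how the mechanism works and are not estimates of bias in this trial.

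**What to change.** - Flag for each registry patient whether every randomisation criterion other than willingness to be randomised was met.
- Define study type with three levels: randomised; eligible but not randomised because of patient or surgeon preference; ineligible.
- Run the treatment × study-type interaction, and any pooling, on the first two levels only. Report the ineligible group separately.
- Describe the series as consecutive consenting patients rather than uninterrupted. An anonymous count per centre of LLS patients not enrolled would show how complete it is.

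The cost is at most one CRF field, a count per centre and some rewording. The real downside is a smaller registry group in the interaction and pooled analyses, and so less precision there.
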